
## Qualitative and mixed-methods analysis

*Qualitative data analysis* will explore the acceptability of the intervention, the extent to which participants and helpers engaged with it, perceptions of how the intervention influenced behaviour, the value of helpers’ support and contextual factors. Qualitative data will be analysed by two researchers who will independently code using Braun and Clarks’ approach to thematic analysis.^73^ The resulting coding framework will be discussed between researchers and also within the larger study team to finalise meaningful themes and subthemes. Twenty per cent of the interviews will be double coded. Disagreements will be resolved by discussion. The analyses will test the hypothesised causal pathways expressed in the logic model and will also develop the intervention’s theory of change where little is currently known (eg, how social support and web-based goal monitoring operate together to change health behaviours). This will inform the study design of any future trial by determining which elements of the intervention work well for health behaviour change in participants, how they interact with each other and which need adjustment or further development.*Analysis of the logic model* will be conducted using the following mixed-methods data integration strategies. Qualitative data, intervention usage statistics and Social Network Analysis data will be collected and analysed as separate data sets in the first instance. The three sets of data will then be mapped onto the logic model and triangulated with each other for complementarity (where data build up a more integrated picture of how the intervention works) and also to identify any disagreements between data sets. Depending on time and resources, the following steps will be undertaken to resolve potential disagreements in data: (i) disagreements between sets of data will be resolved using the four strategies identified by Pluye *et al;*^74^ and (ii) any questions arising from a data set at this point an assessment will be made about whether these question(s) could be resolved or themes further explored by interrogating data from another data set (the ‘following a thread’ method).^75^ An ‘interpretive rigour’ checklist^75^ will be used to optimise the rigour of interpretation and meta-inferences made in producing the final logic model drawing on the three data sets.

All quantitative analyses will be performed in SAS for Windows V.9.3 and/or R for Windows V.3.2.2, or higher versions of these programs. Qualitative analyses will be performed using NVivo 10.

### Sample size

We intend to recruit 120 participants. Since we are most interested in the intervention, we will recruit using a 2:1 ratio with 80 participants in the intervention group and 40 in the control group. We expect a dropout rate of 30%. This final sample size of 84 for analysis is not powered to detect any differences between groups for the proposed effectiveness outcomes (BMI, physical activity and diet) but will provide enough precision to estimate any feasibility proportion (eg, proportions retained/found the study acceptable/provided outcome data) across the whole sample to within ±11 percentage points using a 95% CI. This would also allow for the estimation of the mean of a continuous outcome (such as BMI) in the intervention arm to within 0.262 of an SD.

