5. Are appropriate retention rates achieved at 12-month follow-up?	Measured using the following scale in both the intervention and control group at 12 months: if>70% followed up, proceed; if 50%–69% followed up, discuss with TSC; if<49% followed up, do not proceed
6. Do the majority (>50%) of participants within the intervention group visit the app at least twice or do 25% of participants randomised use it three or more times?	App usage statistics and/or participant interviews
7. Do the data collection procedures effectively collect the data required for a full trial? Successful completion of *at least one* data collection method (BMI, physical activity *or* healthy eating) at both baseline and at 12 months in those retained measured using the following scale:	If>90% *of at least one* data collection measure completed, proceed If 70%–89% *of at least one* data collection measure completed, discuss strategies for improvement in future trial with TSC If<70% *of all three* data collection measures completed, do not proceed without further modification and pilot
8. Are the intervention costs of a full trial covered?	Identification of a source to pay access and treatment costs

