## Quantitative analysis

A detailed Statistical Analysis Plan has been drafted and will be finalised before the study statisticians are given access to the study group allocations.*Baseline characteristics* will be summarised overall and by randomised group. Participant characteristics will be summarised in relation to socio-demographic, lifestyle, occupational, health status and quality-of-life variables.*Feasibility measures* will be the primary focus of the analysis. Follow-up rates at 12 months will be reported overall and by randomised group, with 95% CIs. The association between baseline factors and follow-up will be assessed using logistic regression, with follow-up (yes/no) as the response variable. A multivariable regression model will be developed to identify independent predictors of follow-up. Use of the intervention will be summarised for the intervention group, overall and in relation to selected baseline characteristics. The availability and utility of data relating to data usage for the app and website will be explored, and a range of summary measures will be presented in the final statistical outputs.*Efficacy outcomes* will be summarised overall and by randomised group, and compared using linear regression models, with randomised group, the baseline measurement of the outcome, age and gender as predictor variables. Regression models will also adjust for the minimisation factors. The residuals from each regression model will be assessed for normality. Where necessary, the outcome measure (at follow-up and at baseline) will be transformed to improve model fit. All analyses will be conducted under intention-to-treat principles and complete case analysis used, unless >20% of cases are lost due to missing data, in which case multiple imputation will be performed. These analyses are exploratory and underpowered, so no formal hypothesis testing will be performed but effect sizes will be reported in line with Consolidated Standards of Reporting Trials guidelines for reporting feasibility and pilot studies (http://www.bmj.com/content/355/bmj.i5239).*Process evaluation measures* will be descriptively analysed to summarise use of the app and website. A per-protocol analysis will also be conducted using simple proxies for adherence (eg, website login/% of webpages accessed) in order to identify the treatment effect associated with adherence.*Potential mediators of change*, such as social support, motivation and self-efficacy, will be used in an exploratory mediation analysis to assess whether they might lie on the causal pathway and to test the logic model.^68^ This will assist in the decision as to whether we need the mediation measures in a future full trial.*Social Network Analysis* will be performed on participant sociograms and egocentric questionnaires. Sociogram data will be captured using pen and paper and later transferred to an ego-network software package such as VennMaker or EgoNet. Data will then be exported for analysis. We will calculate network measures on the alter level (eg, homophily) and the network level (size, density, EI-Index, diversity, components, proportions of ties with specific attributes). Multivariate analyses will then be run on both alter and network level data.*The cost data* will be summarised and described using mean values and variation around these estimates. Key fixed and variable costs of developing the intervention will be described and summarised. EQ-5D and ICECAP-A outcome data will be reported by within-attribute response rates, mean values and associated variance. Within-trial economic analyses will be performed using STATA V.12.0 and reported in line with recent CHEERS guidelines^69^ and the UK public health reference case.^70^ Missing data will be handled using multiple imputation (for both cost and outcome data).^71 72^ Cost–utility estimates will be presented on a cost-effectiveness plane using the UK’s threshold for willingness to pay for an incremental quality-adjusted life-year.

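### The ±11-point precision is worked out on the 84 expected completers but claimed for retention, whose base is the 120 randomised, and it does not describe control-arm retention

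*Protocol article*

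**What the plan says.** The Sample size section of the protocol article gives the inputs in sequence. "We intend to recruit 120 participants", and "we will recruit using a 2:1 ratio with 80 participants in the intervention group and 40 in the control group". A 30% dropout is then expected, which leaves 84. The section states that "This final sample size of 84 for analysis is not powered to detect any differences between groups", but that it is enough "to estimate any feasibility proportion (eg, proportions retained/found the study acceptable/provided outcome data) across the whole sample to within ±11 percentage points". Retention is the first of the three examples in brackets. The next sentence gives a precision of 0.262 SD for a mean in the intervention arm.

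Table 2 (progression criteria) sets the retention scale in criterion 5, measured "in both the intervention and control group at 12 months": above 70% proceed, 50% to 69% discuss with the Trial Steering Committee (TSC), below 49% do not proceed. The Quantitative analysis section adds: "Follow-up rates at 12 months will be reported overall and by randomised group, with 95% CIs". Criterion 6 (app use) concerns the intervention group. Criterion 7 (data completeness) is assessed among those retained.

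**The concern.** The 84 are the people left after dropout. A retention proportion cannot be estimated among people already selected for being retained; its base is everyone randomised. The sentence therefore applies one n to quantities with different denominators.

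The precision is also given for the whole sample only, while criterion 5 is measured in both groups and follow-up is to be reported by group. With 2:1 allocation the control arm is small, and the planned retention of 70% falls at the boundary between proceeding and discussing. A TSC member who carried ±11 over to the control arm would take that arm's rate to be better determined than it will be.

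**Working it through.** **Inputs.** From Sample size: 120 randomised, 80 and 40 by arm, 30% dropout. Expected retained: 120 × 0.7 = 84, 80 × 0.7 = 56, 40 × 0.7 = 28. The article does not state the assumed proportion. I take 0.5 as the worst case and 0.7 as the planned retention.

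**Reproducing the plan's figures.** The 95% half-width is 1.96 × √(p(1−p)/n). With n=84 and p=0.5: 1.96 × √(0.25/84) = 0.107, or 10.7 points, which rounds to 11. As a cross-check, 1.96/√56 = 0.262, which matches the stated SD figure. Both statements therefore use the numbers expected after dropout.

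**The same formula on each quantity's own denominator (percentage points).**

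| Quantity | n | p = 0.5 | p = 0.7 |
|---|---|---|---|
| Retention, overall | 120 | ±8.9 | ±8.2 |
| Retention or app use, intervention arm | 80 | ±11.0 | ±10.0 |
| Retention, control arm | 40 | ±15.5 | ±14.2 |
| Study acceptability, data completeness (those retained) | 84 | ±10.7 | ±9.8 |
| App acceptability (retained intervention arm) | 56 | ±13.1 | ±12.0 |

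For example, control-arm retention at 0.7 is 1.96 × √(0.21/40) = 0.142. App use at the 25% mark in criterion 6 is 1.96 × √(0.1875/80) = 0.095.

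The last row rests on an assumption. The article does not say which arm completes the USE questionnaire on the app and website at 12 months. Controls get access only after 12-month follow-up, so I take the raters to be the retained intervention participants. The ±12 to 13 holds for mid-range proportions; at p=0.9 it falls to ±7.9.

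**Wilson 95% intervals at the planned 70% retention.**

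- Overall, 84/120: 61% to 77%.
- Intervention arm, 56/80: 59% to 79%.
- Control arm, 28/40: centre (0.7 + 3.84/80)/(1 + 3.84/40) = 0.682; half-width 1.96 × √(0.21/40 + 3.84/6400)/(1 + 3.84/40) = 0.137; interval 55% to 82%.

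The control-arm interval covers 55% to 69% of the band for discussion, about 14 of its 19 points, and runs 12 points above the 70% cut-off.

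**The case against.** The best defence is that the sentence is true as written. It promises precision no worse than 11 points and limits itself to the whole sample. On the correct base of 120, overall retention is estimated to ±8.2 to ±8.9, inside that bound. The other two examples, study acceptability and provision of outcome data, can be taken over both arms among those retained, so 84 suits them. Criterion 6 and intervention-arm retention, on 80, reach ±11.0 at most, and criterion 7, on those retained, ±10.7. All of this stands.

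It is also fair that the harm is limited. Confidence intervals for follow-up will be reported by group, the TSC makes its assessment after the analysis, and the planning half-width enters no decision rule. Criterion 1, which uses the USE questionnaire, has no numeric cut-off for ±12 to 13 to be set against.

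A reader might infer more than the article supports:

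- That the ±11 is an arithmetical error. It is not; it reproduces.
- That it overstates precision for overall retention. It understates it.
- That retention is read in one arm only. Table 2 names both groups and the analysis section adds the overall rate.
- That each arm must pass criterion 5 separately. Table 2 does not say so.

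The defence does not remove two things: retention is listed first under an n that cannot be its denominator, and nothing in the precision statement describes the control-arm rate that criterion 5 calls for.

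**Conclusion.** The point holds as a misapplied denominator and an incomplete precision statement. For overall retention the stated ±11 is conservative by about 2 to 3 points (11 − 8.9 = 2.1; 11 − 8.2 = 2.8). For control-arm retention, which the sentence does not claim to cover but criterion 5 uses, ±11 would be too narrow by about 3 to 4.5 points (14.2 − 11 = 3.2; 15.5 − 11 = 4.5). App acceptability among about 56 people would exceed it by 1 to 2 points at mid-range proportions.

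These sizes assume the planned 120 with an 80:40 split, equal 30% dropout in both arms, proportions between 0.5 and 0.7, and the normal approximation for the half-widths. The conclusion does not extend to the choice of 120 participants, the planned analyses or the progression thresholds.

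**What to change.** Restate the precision sentence by denominator, and replace the phrase that claims it for any feasibility proportion:

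- overall retention, n=120: ±8 to 9 points;
- intervention-arm retention and app use, n=80: up to ±11;
- control-arm retention, n=40: ±14 to 15;
- study acceptability and data completeness among those retained, n=84: ±11;
- app acceptability, where summarised as a proportion in the roughly 56 retained intervention participants: ±12 to 13.

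State the assumed proportions (0.5 and 0.7) beside the figures.

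The change is to text only and needs no extra participants. Its small cost is that the control-arm and app-acceptability figures look less favourable than ±11, while overall retention looks better.

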### Data management

To ensure safe and accurate data management, the study team will adhere to the agreed HelpMeDoIt! Data Management Plan. All study data will be gathered by trained researchers using hardcopy paper questionnaires and stored in a locked filing cabinet within our secure research unit. Data will then be entered by approved study personnel onto a secure online database (developed and hosted by the Robertson Centre for Biostatistics, University of Glasgow). Data will be entered using a unique participant ID so that study personnel remain blinded to group allocation. Appropriate elements of the database have automated error checking facilities to ensure only valid data are entered. We will perform single data entry, of which 10% will be cross-checked by double entry. Full double data entry will be performed if >5% error rate is detected. The study team and staff performing data entry work closely together within the same research unit, enabling quick identification and rectification of any errors. Qualitative data will be anonymised in all interview transcripts.

Several strategies will be employed to minimise sources of data bias, including random allocation of participants, retention methods to reduce loss to follow-up, restriction of only one participant per household and researchers completing data collection not involved in either delivery of the intervention or data analysis. All data will be kept for 10 years in line with University of Glasgow Research Governance Framework Regulations for clinical research. These data will be stored confidentially on password-protected servers. The final data set will be accessible by approved members of staff from the research team and Robertson Centre for Biostatistics, University of Glasgow. Approved members of the software company, who have signed a Data Protection Agreement, will have access to limited participant contact details to enable them to effectively manage software errors. The low-risk nature of this study means that a Data Monitoring and Ethics Committee (DMEC) is not required for this feasibility trial. Our Trial Steering Committee will cover the functions of the DMEC, particularly in relation to ethical issues, patient safety and continuation of the trial.

### Data sharing

We will implement the following data sharing policy. Participants will have the option of consenting to the research team sharing their data with other researchers. This would involve their data being stored anonymously with the UK Data Archive (an internationally acknowledged centre of expertise who store research data for use by researchers and scientists). Other genuine researchers may then access these data to help answer future research questions. All information stored adheres to the Data Protection Act 1998. Participants will never be identifiable from the research data. Participants *do not* have to give consent to data sharing to be able to take part in the study.

### Retention of participants

We will attempt to maintain good participant retention using several methods, including giving options for participants regarding where data collection takes place, provision of newsletter updates, sending birthday cards, obtaining mobile numbers and alternate contact details, offering a reduced item version of the follow-up questionnaire to provide at least a minimum data set for participants who are reluctant to complete the full follow-up and £20 voucher payments as a thank you for each point of data collection.

Participants have the right to withdraw consent for participation in the HelpMeDoIt! study at any time. If a participant initially consents but subsequently withdraws from the study, clear distinction will be made as to what aspect of the study the participant is withdrawing from. This could be: (i) withdrawal from the intervention; (ii) withdrawal from follow-up data collection; or (iii) withdrawal from entire study. Any retrospective request for data to be deleted will be respected.

## Ethics and dissemination

Ethical approval for stage 1 was granted by the University of Glasgow MVLS College Ethics Committee (Ref: 200140108). Ethical approval for stage 2 has been granted by the NHS West of Scotland Research Ethics Committee (Ref: 15/WS/0288). Research governance approval has been given by NHS Greater Glasgow and Clyde Health Board. The study will be conducted in accordance with the recommendations for physicians involved in research on human participants adopted by the 18th World Medical Assembly, Helsinki 1964 and later revisions. Findings from this study will be disseminated through multiple peer-reviewed publications and conference presentations. We also intend to participate in public engagement events, for example, via the Glasgow Science Centre.

## Assessment of harms

The intervention is low risk to participants. There is a risk that participants may set unhealthy goals and that helpers may not provide support in a positive way. However, we will provide guidance to helpers to ensure that they are aware of how to provide positive support for participants. We will include information about healthy diet in line with government recommendations as well as advice on safely increasing physical activity levels. Participants will be encouraged to discuss any health concerns with their GP who will be informed of their participation. We will encourage fieldworkers, participants and helpers to report negative outcomes or experiences to the study team (email, telephone or by post) and we will explore the issue of ‘harm’ in the interviews with both participants and helpers.

10.1136/bmjopen-2017-017159.supp3Supplementary data

10.1136/bmjopen-2017-017159.supp4Supplementary data

10.1136/bmjopen-2017-017159.supp5Supplementary data

10.1136/bmjopen-2017-017159.supp6Supplementary data

10.1136/bmjopen-2017-017159.supp7Supplementary data

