Promote autonomy	Encourage customisation of goals Ability to add own goals Encouragement and advice via daily app messages/tips Website and app designed in an autonomy supportive way Personalisation of settings	Guidance on website to support participant to set own goals in an autonomy supportive way Encouragement and advice via daily app messages/tips
Provide social support (instrumental and emotional)	Guidance on website Encouragement and advice via daily app messages/tips	Guidance on website Encouragement and advice via daily app messages/tips
Support ongoing goals around physical activity, diet and well-being	Guidance on website Encouragement and advice via daily app messages/tips	Guidance on website Encouragement and advice via daily app messages/tips

Overall, the website will provide evidence-based information for participants and helpers on healthy eating, physical activity and guidance on how to select and/or be a good helper (see below for details). The app will be used to set and monitor weight loss goals, and as a platform to promote interaction with nominated helpers. Example screenshots from the app and website are provided in the online supplementary appendices 3–7.

The HelpMeDoIt! intervention will be delivered via a smartphone app and website. The core aspect of the intervention involves participants nominating one or more ‘helpers’ from among people they know to support them with their weight loss goals. Overall, the intervention will have seven key elements, including: (i) support for goal setting and planning; (ii) ‘track your progress’ for monitoring; (iii) ‘nominate your helper’ to identify social support; (iv) obtain agreement from nominated helper(s) to provide support; (v) helper-specific advice on how to provide effective support; (vi) behaviour-specific information (including ‘tips’ and case stories); and (vii) the goal updates and support element of the intervention.

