### The control group

The control group will receive a leaflet about the health benefits associated with healthy eating and physical activity behaviour change. They will not receive any social support or personalised content. Participants in the control group are not restricted in any way regarding their involvement in other weight loss activities. They can continue to embark on weight loss strategies, for example, join a slimming club. Controls can access the website and app after follow-up is complete at 12 months.

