#### Qualitative interviews with participants 

At 6 months, we will interview up to 30 participants (depending on data saturation). Participants will be purposively sampled for a range of characteristics (eg, level of app/website use, age, gender). We will also specifically seek to interview those who did not take up the intervention to explore the reasons for this. At 12 months, we will also interview up to 20 participants (10 participants who continued to use the website/app after 6 months, and 10 who ceased to use it). Semistructured interview guides will be used at both time points to explore participant insights related to acceptability of the outcome measures, acceptability and usability of the app and website, patterns of usage, impact of the intervention on behaviour, support received from helpers and barriers to use. Mediators of change will also be explored in the qualitative interviews.

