#### Qualitative interviews with helpers 

At 6 months, we will interview up to 20 helpers, purposively sampled for a range of characteristics (eg, level of app/website use, age, gender). A semistructured interview guide will be used to explore helper insights related to acceptability, guidance provided for being a helper, types of support provided to their friend, challenges of supporting their friend and/or using the app and website, and changes in their own health behaviour as a result of being a helper.

Interviews will be completed by trained researchers via the telephone or face to face at a preferred venue (eg, their home or university). Interviews will be audio recorded and transcribed verbatim. A separate informed consent process will take place for the qualitative interviews.

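### Harms are captured only by encouraged reports and interviews, which reach further into the intervention arm, so reported rates should not be compared between arms without one common question

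*Protocol article*

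**What the plan says.** The Assessment of harms section calls the intervention low risk and names two hazards: participants may set unhealthy goals, and helpers may support them badly. It then gives two capture routes. The first is voluntary reporting: "We will encourage fieldworkers, participants and helpers to report negative outcomes or experiences to the study team". The second is exploration of harm "in the interviews with both participants and helpers".

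Helpers belong to the intervention. The section on the intervention group states: "The core aspect of the intervention involves participants nominating one or more ‘helpers’ from among people they know to support them with their weight loss". Of controls, the protocol says "They will not receive any social support or personalised content" and "Controls can access the website and app after follow-up is complete at 12 months".

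The interview plans are as follows:

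- **Helpers:** "At 6 months, we will interview up to 20 helpers, purposively sampled for a range of characteristics".
- **Participants at 6 months:** up to 30, with app or website use as one sampling characteristic among others, and with a specific search for people who did not take up the intervention. The split by arm is not stated.
- **Participants at 12 months:** up to 20, half of whom kept using the website or app after 6 months and half of whom stopped.
- **Controls:** Table 4 assigns a question about the control arm to participant interviews, without a number.

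Table 3, presented as the complete set of measurable outcomes, has no harm item. The Data management section gives the Trial Steering Committee the functions of a data monitoring committee, "particularly in relation to ethical issues, patient safety and continuation of the trial".

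**The concern.** A route that depends on someone choosing to speak has no denominator. If a participant reports nothing, the trial cannot say whether nothing happened or nobody asked. That holds in both arms.

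The routes also differ by arm. An intervention participant may be the subject of a report from one or more helpers, of a helper interview, and of a 12-month interview selected on app use. A control has no counterpart to these three. If these routes bring up any harm that would otherwise go unreported, the reported rate rises in the intervention arm alone. An excess there could then not be told from better detection.

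This matters to the Trial Steering Committee, which will read whatever reports arrive while responsible for safety and continuation. It also matters to the purpose of the study. A feasibility trial is the place to try out the harms procedure of the full trial, and as described this one would finish without having tried a uniform one.

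**Working it through.** **The plan's own figures.** The documents give no harm rate, harm count or reporting probability. The nearest figures are the precision statements under Sample size, and they reproduce: 120 × 0.70 = 84 analysed; 1.96 × √(0.25/84) = 0.107, stated as ±11 points; 80 × 0.70 = 56, and 1.96/√56 = 0.262 SD. The point does not depend on them.

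**Routes by arm, from the text.**

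| Route | Intervention | Control |
|---|---|---|
| Participant's own report | yes | yes |
| Fieldworker passing on what is heard | yes | yes |
| Helper report | yes | no |
| Helper interview at 6 months (up to 20) | yes | no |
| Participant interview at 6 months (up to 30) | yes | possible, number not stated |
| Participant interview at 12 months (up to 20) | yes | in effect no, as selection is on app use and controls have no access until follow-up ends |
| Same harm question put to everyone | not described | not described |

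**Size, under assumptions.** Let s be the probability that a harm is reported by the routes common to both arms. Let h be the probability that it is reported, independently, through a helper; h already allows for participants whose helper is absent or inactive. Interviews are left out. With equal true rates, capture is 1 − (1 − s)(1 − h) in the intervention arm and s in the control arm, so

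ratio of reported rates = [1 − (1 − s)(1 − h)] / s.

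Both s and h are my assumptions, taken as 0.3 to 0.8 and 0.1 to 0.5:

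| s | h | Intervention capture | Control capture | Ratio |
|---|---|---|---|---|
| 0.3 | 0.1 | 0.37 | 0.30 | 1.23 |
| 0.3 | 0.3 | 0.51 | 0.30 | 1.70 |
| 0.3 | 0.5 | 0.65 | 0.30 | 2.17 |
| 0.5 | 0.1 | 0.55 | 0.50 | 1.10 |
| 0.5 | 0.3 | 0.65 | 0.50 | 1.30 |
| 0.5 | 0.5 | 0.75 | 0.50 | 1.50 |
| 0.8 | 0.1 | 0.82 | 0.80 | 1.025 |
| 0.8 | 0.3 | 0.86 | 0.80 | 1.075 |
| 0.8 | 0.5 | 0.90 | 0.80 | 1.125 |

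With h = 0 the ratio is exactly 1.00.

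**In participants.** Assume a true harm rate of 10% in both arms, s = 0.5 and h = 0.3. Expected reported rates are 0.10 × 0.65 = 6.5% and 0.10 × 0.50 = 5.0%, or 5.2 of 80 against 2.0 of 40. Equal capture would give 4.0 of 80 against 2.0 of 40. Two things follow. Raw counts differ 2:1 from allocation alone, so only rates are meaningful. And the expected excess is 5.2 − 4.0 = 1.2 reports, so chance could easily hide or exaggerate it.

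**The case against.** The strongest reply is that the protocol plans no comparison of harms between arms. Neither the Quantitative analysis section nor the Assessment of harms section describes a harm count or rate by group. What is set up is signal detection and qualitative exploration. That stands: a reader might infer that the plan builds in a biased harms analysis, and the documents do not support that. The bias bites only if someone makes or infers the comparison. The missing denominator remains either way.

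Second, the named hazards are largely specific to the intervention. Helper-related harm cannot arise in someone with no nominated helper, so equal true rates is not the right premise for it, and asking helpers about it is sensible. That also stands. Helper reports should be kept; they should not feed a comparison.

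Third, a reader might infer that controls are left out. They are not. They may report, fieldworkers see both arms, and Table 4 assigns control-arm and contamination questions to interviews. The General Health Questionnaire, EQ-5D and resource use are also collected alike in both arms at baseline and 12 months. None of these is designated as a harm measure, however.

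Fourth, a reader might infer that the intervention arm will certainly show more harms. The text does not support that: helpers may add nothing, engagement may be low, and events will be few.

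Finally, an article condenses the full protocol, which may hold an adverse event form. That limits what can be said about absent detail. But the article does state its harms method, and the imbalance lies in what is stated.

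**Conclusion.** The point holds in a limited form. As described, harm capture relies on encouraged reports and interviews, is not systematic in either arm, and reaches further into the intervention arm by design. The direction follows from the text on one condition: helpers or interviews must bring up at least some harms not otherwise reported. The size does not follow from the text. Over the assumed range, and counting the helper route only, the ratio of reported rates at equal true rates is about 1.0 to 2.2.

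No planned analysis is invalidated. The risk is that an uninterpretable difference, or an uninterpretable silence, is read as evidence on safety by the Trial Steering Committee or by those designing the full trial. In a low-risk feasibility study this is a correction worth making because it is cheap.

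**What to change.** Put one identical structured question to every participant in both arms at the existing 12-month face-to-face visit: any negative outcome or experience since baseline, yes or no, with free text. Keep it in the reduced-item follow-up form described under Retention of participants, so that it is not lost among those who decline the full questionnaire.

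Base any by-arm statement about harms on the rates from this question, with the number asked as denominator. Keep spontaneous, helper and interview reports as signal detection, listed separately by source and without comparing arms.

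The cost is one extra item and one extra table, with no added visit. There are two limits. The question covers only those followed up, and it will be imprecise by arm. At the expected 30% dropout, 56 and 28 participants would answer, so the 95% half-width at a proportion of one half is 1.96 × √(0.25/56) = ±13 points and 1.96 × √(0.25/28) = ±19 points. It makes capture comparable among those followed up; it does not make a small trial informative about rare harms.
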